### Ancillary and post-trial care

All study subjects are critically ill and as a result will receive close monitoring as part of their standard of care prior, during, and after study participation.

### Reducing bias

Risk of selection bias will be reduced by concealed randomization using variable and undisclosed blocks. The clinical team (ICU physicians, nurses, allied health care providers), patients and family members, all research personnel, and outcome assessors and adjudicators will be blinded. Research pharmacy personnel will not be blinded as they are preparing the study drug; however, they will remain independent of the clinical team. Accordingly, decisions to discontinue life-sustaining therapies and other outcomes that require subjective assessments will not be affected by individually held beliefs regarding the effects of midodrine. In addition, we will record co-interventions to detect potential performance bias.

Finally, our biostatisticians and analysts will be blinded to allocation to ensure that blinded analysis is performed and remains in keeping with our pre-specified analytic plan.

### Substudies and secondary analyses

There are currently no substudies planned for the LIBERATE trial. However, any proposed substudies will be presented to the Executive Committee and require unanimous approval. They will then be presented to the Steering Committee and will require majority approval prior to proceeding.

### Statistical analyses

All patients will be analyzed as randomized in accordance with the intention-to-treat principle. However, we will also plan a secondary efficacy analysis including patients who received all study drug doses (per protocol analysis). The criterion for statistical significance will be based on alpha = 0.05. All tests will be two-sided, and all analysis will be performed using STATA v16 or later.

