### Trial interventions

#### Experimental arm

Patients in the experimental arm will receive midodrine 10 mg, administered enterally, q8h from time of study inclusion to 24 h post-IV vasopressor support termination. This will be administered as a capsule containing the active substance.

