#### Control arm

Patients in the control arm will receive a placebo, administered enterally, q8h from time of study inclusion to 24 h post-IV vasopressor support termination. This inactive substance will be administered as a capsule that appears identical to the midodrine capsule.

The administration of capsules will be the responsibility of the blinded bedside nurse. There is no maximum duration of study treatment.

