#### Primary outcome measure

The primary outcome is:
The length of ICU stay as measured in hours. We will include both timing of discharge decision and actual departure from ICU.

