### Data analysis

#### Patient-centered analysis

All analyses will follow the intention-to-treat (ITT) principle. Analyses of the primary and secondary outcomes (i.e., patient-centered outcomes) will involve summary measures obtained by aggregating the endpoints using Stata software package (StataCorp, TX, USA). We will compare median differences along with their 95% confidence intervals. Baseline comparisons will be performed using the chi-squared test for equal proportions with results to be reported as numbers, percentages, and 95% confidence intervals. Continuous normally distributed variables will be compared using paired *t*-tests and reported as means with 95% confidence intervals, while non-normally distributed will be compared using Wilcoxon rank sum tests and reported as medians and interquartile ranges.

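### The per-protocol set requires every dose, but the number of doses depends on how long vasopressors run after randomisation, so the set favours short courses and its contrast can be biased in either direction

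*Protocol article*

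**What the plan says.** The Statistical analyses section makes intention to treat the main approach: "All patients will be analyzed as randomized in accordance with the intention-to-treat principle". It then adds that "we will also plan a secondary efficacy analysis including patients who received all study drug doses (per protocol analysis". No tolerance, share of doses or time window is attached. The same paragraph sets the significance level once, for everything: "The criterion for statistical significance will be based on alpha = 0.05".

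The Experimental arm section gives the course of study drug as "q8h from time of study inclusion to 24 h post-IV vasopressor support termination". The Control arm section applies the same rule to placebo and adds: "There is no maximum duration of study treatment".

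The primary outcome is ICU length of stay in hours. Duration of IV vasopressor support is listed under Secondary outcome measures. The Discussion expects shorter vasopressor treatment to lead to shorter ICU care.

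The Patient-centered analysis section says: "All analyses will follow the intention-to-treat (ITT) principle". Read literally, that leaves no room for the per-protocol analysis.

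**The concern.** With a fixed course, every patient has the same number of doses to miss. Here the course lasts as long as the vasopressors plus 24 h. A patient who weans in half a day must take a handful of doses to qualify; one who needs vasopressors for a week must take about 25. Requiring all of them selects on something that happens after randomisation and that the drug is meant to change.

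This goes beyond the ordinary weakness of per-protocol sets. Membership depends directly on a secondary outcome and, through it, on the primary one. The result would be reported as an efficacy analysis, under the same 0.05 criterion, for a set tilted towards fast recoverers and possibly tilted by different amounts in the two arms.

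**Working it through.** **Inputs from the article.** Dosing interval 8 h; dosing ends 24 h after vasopressors stop; no cap; 175 patients per arm; two-sided alpha 0.05, so 2.5% per side; design effect a 20% reduction in stay.

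**Inputs that the article does not give, so assumed.** The missed-dose rate, the distribution of vasopressor duration and its correlation with ICU stay. Ranges are shown for the miss rate and the correlation.

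**Step 1: doses needed.** With T hours of vasopressors after inclusion and a first dose at time 0, doses = floor((T + 24)/8) + 1. For T = 12: 36/8 = 4.5, so 5 doses. For T = 72: 96/8 = 12, so 13 doses. For T = 168: 192/8 = 24, so 25 doses.

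**Step 2: chance of qualifying.** If each dose is missed independently with probability p, the chance is (1 − p)^doses.

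| Vasopressors after inclusion | Doses | p = 1% | p = 2% | p = 5% | p = 10% |
|---|---|---|---|---|---|
| 12 h | 5 | 0.95 | 0.90 | 0.77 | 0.59 |
| 72 h | 13 | 0.88 | 0.77 | 0.51 | 0.25 |
| 168 h | 25 | 0.78 | 0.60 | 0.28 | 0.07 |

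Adherence per dose is the same down each column; only the length of the course differs.

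**Step 3: no drug effect, 175 per arm.** Simulated trials, with a two-sided rank-sum test in the retained patients. Assumptions: vasopressor duration lognormal, median 36 h, log-SD 0.9; ICU stay lognormal, median 144 h, log-SD 0.71; correlation 0.6 or 0.3. The log-SD of 0.71 is compatible with the plan's 161 per arm: 2 × (1.96 + 0.84)² × 0.7146² / (ln 0.8)² ≈ 161.

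| Missed per dose, midodrine vs placebo | Retained | Median stay retained (correlation 0.6) | Wrong-conclusion rate on one side |
|---|---|---|---|
| 3% vs 3% | 75% vs 75% | 135 vs 135 h | about 2.5% (nominal) |
| 5% vs 2% | 62% vs 82% | 131 vs 138 h | false benefit about 8%; about 5% at correlation 0.3 |
| 8% vs 2% | 48% vs 82% | 125 vs 138 h | false benefit about 17%; about 7% at correlation 0.3 |
| 2% vs 5% | 82% vs 62% | 138 vs 131 h | false harm about 8 to 9% |

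In the third row the apparent reduction is 1 − 125/138 ≈ 9%, against a design effect of 20%.

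**Step 4: true effect, equal miss rates.** This is a separate large simulation: the same vasopressor distribution, an independent remaining ICU time with median 60 h and log-SD 0.6, and vasopressor time 30% shorter on midodrine. The intention-to-treat difference in median stay is about −12.7 h. In the all-doses set it is −11.1, −9.3 and −7.2 h at 2%, 5% and 10% missed. The restriction keeps short courses, where there are fewer hours to save.

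**The case against.** Four points can be made in the plan's defence.

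- **The analysis is secondary.** Intention to treat is the main analysis, and neither the primary result nor the sample size depends on the per-protocol set. This stands and limits the weight of the point.
- **The sizes rest on assumed inputs.** This stands too. The 8% vs 2% case is a fourfold difference between arms, and halving the correlation cuts its false-benefit rate from about 17% to about 7%. Bedside nurses are blinded, and the article gives no rule that would make doses be held more often in one arm. Monitored events such as hypertension and bradycardia make unequal adherence possible, not established.
- **Adherence definitions are often left to the analysis plan.** This does not answer the point, because the article itself fixes the definition as all doses.
- **Any per-protocol set is selected after randomisation.** True, but here the qualifying hurdle itself grows with an outcome, and a different definition can avoid that.

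A reader might also infer that full dosing cannot be verified, because daily adherence data stop at ICU discharge or day 30. The article does not support that. Table 2 marks protocol violations at every time point, and the section on intention to treat and ineligible patients says that reasons for deviations will be recorded.

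**Conclusion.** The point holds as a defect in a stated secondary definition. That the set over-represents short vasopressor courses follows from the dosing rule and the all-doses requirement, as long as some doses are missed and the chance of missing one does not fall sharply as the course lengthens.

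The consequence for the comparison between arms is conditional. With no effect and equal miss rates it stays null. With unequal rates it can favour either arm: in the scenarios tried, the one-sided error is about 5 to 17% instead of 2.5%. With a true effect and equal misses it understates the benefit.

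A reader might infer that the analysis would manufacture a benefit for midodrine and so rescue a null main result. The article does not support that: it needs more missed doses on midodrine, and nothing in the article shows that this will happen. The primary analysis is untouched.

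**What to change.** Change the wording before unblinding:

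1. Define the per-protocol set by criteria that do not depend on the length of treatment. One example is patients eligible at randomisation who received all doses scheduled in a fixed early window, such as the first 24 h. Vasopressors are running at inclusion and dosing continues for 24 h after they stop, so under the stated schedule every patient's planned course covers that window.
2. State that the analysis is supportive only.
3. Reconcile the Statistical analyses section with the Patient-centered analysis section, for example by limiting the intention-to-treat statement to the main analyses.

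A complier-average estimate using randomisation as the instrument is not a fix by itself. It still needs a definition of complier, and if that is all doses the same dependence on treatment length returns.

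The cost is a less strict adherence set, which says nothing about doses missed after the window. No extra patients are needed, and dosing does not change.

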### Sample size

Using an alpha of 0.05 and a power of 80% and assuming a 20% deduction in the length of stay associated with midodrine based on previous pilot work by Anstey et al., we would need a sample size of 161 patients per arm [20]. To compensate for up to an 8% loss to follow-up, we will plan for 175 patients per arm for a total treatment size of 350 patients.

### Data analysis

#### Patient-centered analysis

All analyses will follow the intention-to-treat (ITT) principle. Analyses of the primary and secondary outcomes (i.e., patient-centered outcomes) will involve summary measures obtained by aggregating the endpoints using Stata software package (StataCorp, TX, USA). We will compare median differences along with their 95% confidence intervals. Baseline comparisons will be performed using the chi-squared test for equal proportions with results to be reported as numbers, percentages, and 95% confidence intervals. Continuous normally distributed variables will be compared using paired *t*-tests and reported as means with 95% confidence intervals, while non-normally distributed will be compared using Wilcoxon rank sum tests and reported as medians and interquartile ranges.

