**Methods:**

The LIBERATE study will be a multicenter, parallel-group, blinded, randomized placebo-controlled trial. It will recruit adult (i.e., age ≥ 18 years) critically ill patients receiving stable or decreasing doses of IV vasopressors. Eligible patients will be randomized to receive either midodrine 10 mg administered enterally every 8 h or placebo until 24 h post-discontinuation of IV vasopressors. The primary outcome will be ICU length of stay. Secondary outcomes include all-cause mortality at 90 days, hospital length of stay, length of IV vasopressor support, re-initiation of IV vasopressors, rates of ICU readmission, and occurrence of AEs. Health economic outcomes including ICU, hospital and healthcare costs, and cost-effectiveness will be evaluated. Pre-planned subgroup analyses include age, sex, frailty, severity of illness, etiology of shock, and comorbid conditions.

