### Pre-specified subgroup analyses

Secondary analyses will examine the effects for the length of ICU stay and duration of IV vasopressors within subgroups defined at baseline by age (< 65 vs. ≥65 years), sex, frailty (Clinical Frailty Scale score 1–4 vs. ≥5), severity of illness (quartiles of predicted risk of death from baseline APACHE II score), and types of shock (i.e., septic, hypovolemic, cardiogenic, obstructive or neurogenic). We will also evaluate subgroup based on comorbid conditions (i.e., pre-existing cirrhosis and acute kidney injury on admission). The subgroup analyses will use logistic regression with terms for treatment arm, subgroup, and subgroup by treatment interaction. We hypothesize that midodrine is more beneficial in young patients, in those with lower frailty and illness severity at baseline, those with pre-existing cirrhosis, those with acute kidney injury, and those who meet strict criteria for septic shock.

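### As written, the analysis paragraph applies median differences to every secondary outcome, including mortality, readmission and vasopressor restart, and assigns the only test of proportions to baseline data

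*Protocol article*

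**What the plan says.** The Secondary outcome measures section of the protocol article mixes two kinds of outcome. Lengths of stay and duration of IV vasopressor support are in hours. The others are deaths from any cause by 60 and 90 days, readmission to the ICU, and restart of IV vasopressors; the abstract likewise lists "rates of ICU readmission".

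The Patient-centered analysis section sets its scope in these words: "Analyses of the primary and secondary outcomes (i.e., patient-centered outcomes) will involve summary measures obtained by aggregating the endpoints". The next sentence names a single between-arm measure: "We will compare median differences along with their 95% confidence intervals". It is not limited to any type of outcome.

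The rest of that paragraph covers:

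- **Proportions:** "Baseline comparisons will be performed using the chi-squared test for equal proportions with results to be reported as numbers, percentages, and 95% confidence intervals".
- **Continuous variables:** a t-test if normally distributed; otherwise, "non-normally distributed will be compared using Wilcoxon rank sum tests and reported as medians and interquartile ranges".

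One other model suits a binary response, and it is reserved for subgroups: "The subgroup analyses will use logistic regression with terms for treatment arm, subgroup, and subgroup by treatment interaction". That section applies it to length of ICU stay and duration of IV vasopressors, not to mortality, readmission or restart. The article names no risk difference, risk ratio, odds ratio or test of proportions for these outcomes.

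**The concern.** A median difference suits outcomes in hours. It does not suit an outcome that each patient either has or does not have, because the median of zeros and ones can only be 0 or 1 (with an odd number of patients). The paragraph therefore states a measure that does not fit some of the outcomes in its scope, and attaches the method that would fit to baseline data.

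This matters because the primary outcome is ICU length of stay, which early death or premature discharge can shorten. Mortality, readmission and restart of vasopressors are the listed outcomes that show whether a shorter stay is a true benefit. If the published measure for them is unusable, the actual one will be chosen outside the published text.

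**Working it through.** **Inputs from the protocol article**

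- Sample size section: 161 per arm before loss, 8% loss, 175 per arm, 350 in total.
- Randomization section: 1:1 allocation, stratified by site.
- Statistical analyses section: "The criterion for statistical significance will be based on alpha = 0.05", with two-sided tests.
- Event rates: none given. The Interim analysis plan calls the baseline incidence of death high, without a figure. All rates below are assumptions.

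**The plan's own figure.** 161 / (1 - 0.08) = 175.0 per arm, and 2 x 175 = 350. The inflation for loss reproduces. The 161 cannot be tested, because no standard deviation or baseline stay is given, but nothing here depends on it.

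**Median of a 0/1 outcome with n = 175.** The sample median is the 88th ordered value. It is 1 if at least 88 of the 175 patients have the event, and otherwise 0. The difference in medians between two arms can therefore be only -1, 0 or +1:

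- both observed rates on the same side of 50%: 0;
- observed rates on opposite sides of 50%: -1 or +1.

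**Comparison with proportions.** For assumed true rates p1 (control) and p2 (midodrine):

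- risk difference RD = p2 - p1;
- 95% CI half-width = 1.96 x sqrt[p1(1-p1)/175 + p2(1-p2)/175];
- power = Phi[(|RD| - 1.96 x se0) / se1], where se0 = sqrt[2 x pbar(1-pbar)/175], pbar is the mean of p1 and p2, and se1 is the square root in the half-width.

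Example, 30% v 20%:

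- se1 = sqrt[(0.21 + 0.16)/175] = 0.0460, so the half-width is 1.96 x 0.0460 = 0.090;
- pbar = 0.25, so se0 = sqrt[2 x 0.1875/175] = 0.0463;
- power = Phi[(0.10 - 0.0907)/0.0460] = Phi(0.20) = 58%.

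The distribution of the median difference comes from 200,000 simulated trials per row.

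| Assumed rates | Median diff. 0 | -1 | +1 | RD (points) | CI half-width (points) | Power, proportions |
|---|---|---|---|---|---|---|
| 10% v 5% | 100% | 0% | 0% | -5 | 5.5 | 43% |
| 20% v 12% | 100% | 0% | 0% | -8 | 7.6 | 53% |
| 30% v 20% | 100% | 0% | 0% | -10 | 9.0 | 58% |
| 40% v 25% | 99.6% | 0.4% | 0% | -15 | 9.7 | 85% |
| 45% v 30% | 90.8% | 9.2% | 0% | -15 | 10.0 | 83% |
| 55% v 45% | 16.6% | 82.6% | 0.8% | -10 | 10.4 | 46% |
| 60% v 52% | 70.0% | 29.8% | 0.3% | -8 | 10.4 | 33% |

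The rows at 30% v 20% and 55% v 45% have the same true difference of 10 points. The median difference is 0 in every simulated trial of the first and -1 in most trials of the second. It reflects where the rates lie relative to 50%, not how far apart they are.

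**The case against.** The best defence is that the median sentence names no outcome and sits in a condensed paragraph. The primary outcome and the first secondary outcomes are in hours, where the measure makes sense, and two of the others are already called rates. The paragraph can also be read as a list of methods by variable type, with the reference to baseline a loose lead-in; on that reading "Baseline comparisons will be performed using the chi-squared test for equal proportions" is merely misplaced. An analysis plan that is not shown may settle the matter, and silence in the article on the effect measure would then be no defect.

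Much of this stands. The authors probably meant the outcomes in hours, and the proportions will be available whatever the wording. But the article is not silent: it states a scope covering all secondary outcomes, names one measure for that scope, and assigns the test of proportions elsewhere. An analysis plan that used risk differences would depart from this text.

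A reader might infer three stronger things that the document does not support:

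- **That the median difference is always zero, so the trial cannot show a mortality effect.** It is zero only when both observed rates fall on the same side of 50%. The protocol gives no rates and calls baseline mortality high, so straddling cannot be excluded. The data would also still allow proportions to be compared.
- **That readmission and restart are defined as yes/no per patient.** They are called rates without a per-patient definition, and repeat events are possible. Only mortality is inherently binary.
- **That the simulation measures harm done by the wording.** The power column shows how limited secondary comparisons are at this sample size. The zeros in the low-rate rows follow from the definition of a median.

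**Conclusion.** The point holds as a defect in stated method. Read as written, the paragraph gives mortality, and readmission and restart if counted per patient, a measure that takes only the values -1, 0 and +1 and at no event rate estimates the size of an effect. With both assumed rates at or below 30%, it was 0 in every simulated trial, although true differences were 5 to 10 points. Near or across 50% it jumps, without becoming informative. Which case would apply rests on event rates that the protocol does not give.

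Severity is moderate. The intended meaning is probably narrower than the text, and the primary outcome, sample size and data collection are untouched. The wording still needs correcting, because these outcomes are needed to interpret a shorter ICU stay.

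**What to change.** In Patient-centered analysis:

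1. Restrict median differences to outcomes measured in hours.
2. For death by 60 and by 90 days, any ICU readmission and any restart of IV vasopressors, each counted once per patient, report a risk difference, a risk ratio or both, with 95% CI. Account for site, the randomisation stratum; Mantel-Haenszel is one option, and an equivalent model would serve.
3. Assign the test of proportions to these outcomes rather than to baseline data.

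This takes one or two sentences and no new data. The sample size stays at 350, because it rests on length of stay. The change should be made before database lock and unblinding.

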### Randomization

Randomization will be done as per a computer-generated randomization schedule through a Web-based portal (i.e., Randomize.net). Eligible patients will be randomized in a 1:1 ratio to midodrine or placebo using permuted blocks of undisclosed and variable size. We will stratify randomization by site.

Randomization will be conducted by the study pharmacists after receiving written notification of the patient enrollment from the study team. The study pharmacy will then prepare and dispense the appropriate blinded study treatment.

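### The outcome estimate (median differences) is not tied to one test: the only tests named for continuous variables depend on normality, and one of them, a paired t-test, cannot be run on two independent arms

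*Protocol article*

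**What the plan says.** Three parts of the protocol article bear on the analysis of ICU length of stay in hours, the primary outcome.

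- **Data analysis, Patient-centered analysis.** After naming the primary and secondary outcomes, it says "We will compare median differences along with their 95% confidence intervals". A sentence on baseline comparisons (chi-squared tests) follows. The section then deals with continuous variables. If normally distributed, they are compared by a paired t-test and reported as means. Otherwise, "non-normally distributed will be compared using Wilcoxon rank sum tests and reported as medians and interquartile ranges". It gives no criterion for normality and no method for the interval on the median difference.
- **Sample size.** With alpha 0.05 and 80% power, "assuming a 20% deduction in the length of stay associated with midodrine", the article concludes that "we would need a sample size of 161 patients per arm". It does not say whether the 20% refers to a mean or a median, and it names no test.
- **Study design and Randomization.** The trial has parallel groups: "Eligible patients will be randomized in a 1:1 ratio to midodrine or placebo", stratified by site. Nothing in the design pairs one patient with another.

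**The concern.** The section promises one kind of estimate and offers two tests that are not tests of it. A t-test compares means. A rank-sum test asks whether stays in one arm tend to be longer than in the other. The difference of two sample medians is a third quantity. If these tests cover ICU stay, three things follow.

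1. The primary test depends on a look at the trial's own data, with no stated rule for that look.
2. In the normal branch the result would be reported as means, although median differences were promised, and the test named there cannot be carried out on independent arms.
3. In the other branch the p-value and the reported interval can give different answers on the same data.

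The Interim analysis plan adds to the need for one defined analysis, because it calls for a conditional power for the primary outcome, and that can only be computed for a specified test.

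**Working it through.** **Inputs from the article.** Two-sided alpha 0.05, power 80%, 20% reduction, 161 per arm, 1:1 allocation, 8% loss.

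**Step 1: the plan's own figures.** 161 / (1 − 0.08) = 161 / 0.92 = 175 per arm, 350 in total, as stated. The 161 itself cannot be reproduced, because the article gives no SD, control value or test.

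**Step 2: what 161 implies.** For two means, n = 2(z₀.₉₇₅ + z₀.₈₀)² / d², so d = (1.960 + 0.842) × √(2/161) = 0.312.
- Raw scale: SD / control mean = 0.20 / 0.312 = 0.64. For lognormal data this is a log-SD of √ln(1 + 0.64²) = 0.586.
- Log scale: log-SD = |ln 0.80| / 0.312 = 0.715.

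These back-solved spreads, and the distributions below, are assumptions.

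**Step 3: simulation.** 161 per arm and 6,000 trials per setting. The t-test is unpaired, since the paired form cannot be run. The 95% interval is for the difference of sample medians, with a standard error from order statistics.

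| Assumed stays | Rank-sum p < 0.05 | t-test p < 0.05 | Median interval excludes 0 | Rank-sum and interval disagree | Rank-sum and t-test disagree |
|---|---|---|---|---|---|
| Lognormal, log-SD 0.715, ratio 0.80 | 78.4% | 69.1% | 55.0% | 25.9% | 17.7% |
| Lognormal, log-SD 0.586, ratio 0.80 | 91.8% | 87.7% | 73.4% | 19.6% | 8.1% |
| Gamma, CV 0.64, ratio 0.80 | 82.5% | 88.2% | 58.9% | 25.5% | 8.8% |
| Lognormal, log-SD 0.715, no effect | 5.1% | 4.8% | 4.3% | 4.3% | 5.2% |

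Simulation error is small: for 25.9%, 1.96 × √(0.259 × 0.741 / 6000) is about 1.1 points. In the first row nearly all disagreements run one way: 24.7% are rank-sum significant with an interval that includes zero, and 1.3% are the reverse.

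**Step 4: sensitivity to the interval method.** A separate run (2,000 trials per setting, percentile bootstrap interval) gave rank-sum significance with an interval including zero in 14% of trials at log-SD 0.586 and 20% at 0.71. Rank-sum and t-test disagreed in 8% to 17%. Taking both interval methods together, disagreement at the planned effect is roughly 15% to 25%.

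**Step 5: the other reading.** In the same run, a Hodges-Lehmann interval obtained by inverting the rank-sum test agreed with that test in 100% of trials, as it should by construction.

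**Step 6: does the repair need to respect site?** Under an assumed log-scale site SD of 0.4, the site-stratified rank-sum test kept power near 77%, while the unstratified test fell to 70%. The interval must come from the same stratified test. With 7 equal sites (3,000 trials), the stratified test and an interval inverting the unstratified one disagreed in 2% to 4% of trials at site SD 0 to 0.2, and in 8% to 10% at 0.4.

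**The case against.** The strongest reply is that the article says less than the concern needs.

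- **Scope.** A reader might infer that the plan expressly takes the primary p-value from a t-test or a rank-sum test. It does not: the sentence naming them follows one on baseline comparisons. Coverage of outcomes is the likeliest reading, not a stated fact. This stands. On the narrower reading, however, the section names no test at all for the primary outcome, so the text still needs clarifying.
- **Meaning of median differences.** A reader might infer that test and interval will often disagree whatever is done. That holds only for a difference of sample medians. If the authors mean the Hodges-Lehmann shift, interval and rank-sum test agree. The article does not say which is meant.
- **Which branch.** The promise of medians points towards the rank-sum test for ICU stay, so the t-test branch may never be used. This is fair, but the branch remains in the text.
- **What decides.** A reader might say that no rule settles a conflict. The Statistical analyses section says "The criterion for statistical significance will be based on alpha = 0.05" and "All tests will be two-sided, and all analysis will be performed using STATA v16 or later", which suggests that a test decides and the interval describes. A conflict would then be awkward to report rather than undecided, provided that the test itself is fixed.
- **Power.** A reader might infer that 161 per arm was computed for a different quantity. The article does not show that; the basis is unspecified.
- **Analysis plan.** A full analysis plan, not shown here, may settle the test and the interval method. That would excuse silence. It does not excuse a stated rule that depends on observed normality and includes a test unsuited to the design.

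**Conclusion.** The point holds in a limited form. The article commits its outcomes to median differences, but offers for continuous variables only a normality-dependent choice, one arm of which cannot be executed in a parallel-group trial. Estimate, test and power basis are not fixed to one another.

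The size depends on the reading. For a difference of sample medians at the full 20% effect, rank-sum test and interval conflict in roughly 15% to 25% of trials, and rank-sum and unpaired t-test in roughly 8% to 18%. Under no effect, rank-sum test and interval conflict in only about 5%. For a Hodges-Lehmann shift, the conflict between interval and rank-sum test disappears. The ranges rest on assumed lognormal stays with log-SD 0.59 to 0.715, because the article gives no spread; gamma data fell within or close to them. In each planned-effect setting tried, the chance of a significant result differed markedly between the three analyses, so a single 80% cannot describe them all. The documents do not show that the sample size is wrong.

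**What to change.** In Patient-centered analysis, remove the normality-dependent choice and the word paired for the primary outcome, and name one analysis. For example: ICU length of stay will be compared by a Wilcoxon rank-sum test stratified by site, two-sided at 0.05. The effect will be given as the Hodges-Lehmann shift in hours, with a 95% confidence interval obtained by inverting that same stratified test. Arm medians and interquartile ranges will be shown as description only.

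In Sample size, state the power for that test.

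The cost is mainly wording. The headline estimate becomes a location shift rather than a raw difference of medians, and a single shift in hours describes a proportional 20% reduction only approximately. A standard Hodges-Lehmann interval inverts the unstratified test, so the stratified inversion has to be programmed and specified. No patients, visits or data items are added.
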